### Study variables and measurements

Baseline and post-intervention outcome variables were measured in both the control and intervention groups three times, at the beginning and end of the first academic year (in September 2013 and June 2014), and at the end of the second academic year (in June 2015). Table 1 provides an overview of all variables measured. Anthropometry (weight, height, body mass index, waist circumference, triceps skinfold thickness, percentage of body fat and fat-free mass) was performed in standardized conditions, as extensively described in the MOVI-2 protocol [37].

**Table 1 Tab1:** Study variables

Type of variable	Specific variables
Primary endpoint measures	Anthropometry: weight, height, body mass index, waist circumference, triceps skinfold thickness, percentage of body fat and fat-free mass by bioelectrical impedance analysis
	Academic achievement
Secondary endpoint measures	Attention deficit hyperactivity disorder risk: parents’ and teachers’ report using the Attention Deficit Hyperactivity Disorder Rating Scale-IV
	Motor skills: fine motor skills, throws and catches, and balance (static and dynamic), assessed by the Movement Assessment Battery for Children
	Health-related quality of life: children’s (by interview) and parents’ (self-administered) report, using the Kiddy-Kindl Questionnaire
	Sleep quality: parents’ report using the Children’s Sleep Habits Questionnaire, accelerometers, children’s sleep diary
Other endpoint measures	Physical activity: parents’ report by the Netherlands Physical Activity Questionnaire, accelerometers
Potential confounding factors	Age
	Sex
	Birthweight
	Breastfeeding: breastfeeding, formula feeding or both (mixed feeding)
	Food consumption: parents’ report, using the Children’s Eating Habits Questionnaire
	Family socio-economic status: education, occupation and socio-economic status index
	Area (urban or rural)
	Origin (native or foreign)

To minimize interobserver variability, the measurements were carried out in the school by trained investigators.

#### Primary outcome measures

##### Anthropometry and body composition

Weight was measured twice (Seca® 861 scales) with the child barefoot and in light clothing. Height was also measured twice, using a wall stadiometer (Seca® 222), with the child barefoot and upright and with the sagittal midline touching the back board. Body mass index was calculated as weight in kilograms divided by the square of the height in metres. Waist circumference was measured three times at the midpoint between the last rib and the iliac crest at the end of a normal expiration and using a flexible tape. Triceps skinfold thickness was measured three times at the triceps using a Holtain Ltd. caliper (0.2 mm accuracy and consistent pressure between valves of 10 g/mm^2^). The percentage of body fat and the fat-free mass were estimated with a four-electrode Tanita® Segmental-418 bioimpedance analysis system (Tanita Corp. Tokyo, Japan). Two readings were obtained in the morning, under controlled temperature and humidity conditions, with the child shoeless and fasting, and after urination and a 15-minute rest. The mean of all the anthropometric measurements was calculated and considered for the analysis.

##### Academic achievement

Basic psychological processes involved in learning (intelligence, cognition, memory, attention and perception) were assessed using the Battery of General and Differential Aptitudes scales for children aged 3–6 years [38] and 6–8 years [39]. Both scales include: (a) global academic predictors (e.g., general intelligence), (b) non-verbal tests (e.g., reasoning and logical puzzle figures), (c) verbal tests (e.g., numerical quantitative concepts) and (d) additional tests (e.g., auditory perception).

#### Secondary outcome measures

##### Attention deficit hyperactivity disorder risk

We used the Attention Deficit Hyperactivity Disorder Rating Scale-IV, which has been translated into a Spanish version and validated [40]. It is a screening and evaluation scale of ADHD that includes two subscales, for inattention and hyperactivity, and a total score. Each item represents each of the ADHD symptoms, according to the criteria of the Diagnostic and Statistical Manual of Mental Disorders [41]. We used the parents’ and teachers’ version, which fits the criterion of ‘the presence of symptoms in at least two environments’.

##### Motor skills

These were assessed by the Movement Assessment Battery for Children [42–44]. This battery has been validated to identify and describe deficiencies in motor performance in children and adolescents from 3 to 16 years old. It consists of eight tests for each age group (3–6, 7–10 and 11–16 years) measuring three dimensions: fine motor skills, throws and catches, and balance (static and dynamic). A higher score indicates better motor performance. It enables classification of: children with motor problems, children with motor risk and children with normal motor development.

##### Health-related quality of life

This is assessed using the Kiddy-Kindl Questionnaire, which has been validated in a Spanish version for children aged 4–7 years and their parents [45]. The Kiddy-Kindl is a generic health-related quality-of-life instrument for children and adolescents, and was developed in Germany for use both in clinical practice and with healthy children. This questionnaire contains 12 questions (with three response options ranging from 1 to 3, where 1 = never, 2 = sometimes and 3 = many times) in six dimensions: physical, emotional, self-esteem, family, friends and school. The children’s version was administered by interview, the parents were offered a self-administered version.

##### Sleep quality

This is assessed using the Spanish version of the Children’s Sleep Habits Questionnaire [46], completed by parents. This instrument focuses on common sleep disorders for children aged 4 to 10 years. The questionnaire allows parents to indicate, for each item, whether they consider sleep habits are a problem for their child. It also includes four questions about the time children go to bed, wake up and get up, and the total number of hours of sleep. Finally, latency, amount, duration of sleep and number of awakenings were also measured by accelerometers (ActiSleep®) in a subsample of 60 schoolchildren. Over a week, children completed a sleep diary.

#### Other study endpoint measures

##### Physical activity

This was evaluated using the Spanish version of the Netherlands Physical Activity Questionnaire [47] for parents, in which they provide information about their children’s daily activity preferences during the six previous months. In addition, children from six schools in the intervention group and another four schools in the control group wore GT3X accelerometers for seven days consecutively (including nights) to measure their physical activity in the first academic year. The accelerometers were programmed in epochs of one second and data will be analyzed using ActiLife software, version 6.1.

#### Confounding variables

Age, sex, birthweight, breastfeeding, food consumption, socio-economic status, living area (urban or rural) and origin (native or foreign) were considered potential confounding variables.

##### Breastfeeding

Mothers were first asked what type of feeding had been chosen during their child’s infancy: breastfeeding, formula feeding or both (mixed feeding). They were also asked up to what age the child was exclusively breastfed and when breastfeeding was completely stopped. In exclusive breastfeeding, the infant received only breast milk without any supplementary feeding.

##### Food consumption

This was estimated using the Spanish version of the Children’s Eating Habits Questionnaire [48], validated for children from 2 to 9 years old. This version was completed by parents.

##### Family socio-economic status

Data regarding family socio-economic status were gathered by using self-reported occupation and education questions completed by either the father or mother. Paternal and maternal education were classified separately as primary education (functionally illiterate, without any studies or those who had not completed primary education), middle education (primary education and high school or secondary education or ‘Bachillerato’) and university education (university degree or Ph.D.). Parental occupation was classified into five categories as follows: (1) supervisor, manager or freelance with ten employees or more, (2) supervisor, manager or freelance with fewer than ten employees, (3) freelance with no staff, (4) unqualified staff and unskilled workers, and (5) household chores, unemployed or others. An index of socio-economic status was calculated using the items regarding parents’ education and occupation. This index distinguishes, according to the scale proposed by the Spanish Society of Epidemiology, five categories of family socio-economic status: lower, upper lower, lower middle, upper middle and upper [49].

### Study intervention

The design of Movi-Kids is based on the social ecological model [50], a theoretical model of behaviour change in which behaviour is understood as the interaction between the physical and social environment. The Movi-Kids programme is a multidimensional intervention aimed at influencing individuals (children, families and teachers) and the environment (including some changes in the physical structure of the playground).

The intervention was applied in the intervention group over two full academic years, and was implemented at three levels:Children participated in an optional extracurricular, play-based, non-competitive physical activity programme (Movi-Kids), adapted to their levels of motor competence (from 4 to 7 years old). The aim of this programme was to increase the weekly physical activity time through three 60 min sessions per week using school facilities. In addition, the Movi-Kids programme included basic sports games, playground games, dance and other activities focused on developing motor skills. At the end of the first year, approximately 90 sessions had been carried out in each school.Parents and teachers included in the intervention group were involved in activities to promote active lifestyles in their children. These activities included: (a) use of reinforcement tools that had demonstrated their utility in improving parents’ and teachers’ compliance and involvement in the programme (e.g., a refrigerator magnet with recommendations for physical activity for children), (b) answering a satisfaction-with-the-programme questionnaire, and (c) access to a blog (http://movi3kids.blogspot.com.es/) where parents could observe their children’s progress, read news regarding reinforcing healthy lifestyles, and ask questions of or make complaints to the research team.Finally, environmental interventions were conducted in the playground. Fixed (a balance circuit and panels with incentives to be physically active during break time) and mobile equipment (tyres of different colours and sizes) were put in the playgrounds to encourage children to be more active during playtime.

The standard physical education curriculum (1 hour per week of psychomotor activities to third-grade preschoolers and 2 hours per week of physical education to first-grade primary schoolers with physical activity levels at low-to-moderate intensity) was applied in both the control and intervention schools because this is compulsory in Spain.

Since this was a cluster-crossover trial, clusters (schools) were randomized to intervention and control groups, with outcomes measured after the first period (first academic year), and then, after a washout period (the summer holidays), clusters crossed over from control to intervention groups, and vice versa.

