### Statistical analysis

The sample size was estimated to be able to show differences between the control group and the intervention group of 2 % (alpha error, 0.05; statistical power, 0.80) in mean body fat at the end of the first year. The estimated sample size was 140 children per group; this figure was multiplied by an inflation factor for cluster-randomized trials [51], which was estimated at 1.1264 using measurements from previous studies in body mass index [52]. To examine subgroup differences (e.g., sex, age, ADHD or socio-economic status) under the same conditions, and estimating a 15 % dropout rate, the minimal sample size was estimated at 1600 children (800 per group).

The statistical analysis will be carried out in two phases. In the first, we will verify that the randomization was effective in creating two comparable groups, examining the differences between the control and intervention groups in mean body fat and academic achievement. After that, we will identify outliers and extreme values, and their trustworthiness. Finally, we will check the adjustment of the variables to the normal distribution by using the Kolmogorov–Smirnov test and graphical procedures (normal probability plot).

In the second phase, we will assess the change between the intermediate and final evaluation variables in the first and second years of the study. Mixed regression models [53] will be estimated using each outcome variable as a dependent variable at the end of the first and second years of the study. The different models will be adjusted for baseline values, age and school (cluster), and the interventions will be treated as fixed affects (1 = intervention group, 0 = control group).

The results will be expressed as absolute differences in change in variables between the baseline and the final measurements (confidence interval of 95 %). When the dependent variable is the prevalence of overweight or obesity, the odds ratio will be calculated, together with a 95 % confidence interval.

Because of the different patterns of weight and height, triceps skinfold thickness and body fat, the models will be separately implemented for boys and girls. A separate analysis will also be conducted for ADHD (with or without), socio-economic status, origin (native or foreign), area (urban or rural), and state-funded or private school.

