Therefore, in considering data on the prevalence of excess weight in Spanish children, taking into account the evidence of the benefits of physical activity for obesity prevention and also considering the behavioural, neurobiological and genetic links between obesity and ADHD, it seems reasonable that an intervention to promote physical activity based on playground games will be useful for simultaneously controlling ADHD and obesity, thereby improving the academic achievement of students with or without ADHD. Therefore, it is expected that our study will provide information on whether the Movi-Kids programme overcomes some of the potential limitations of physical activity interventions in schoolchildren.

Finally, as this was a cluster-crossover design, the length of the trial will be doubled, and some carryover effect cannot be ruled out; however, it has also been suggested that this design is useful for compensating for the loss of efficiency owing to the clustering.

In summary, this study will evaluate the impact of a multidimensional physical activity intervention (Movi-Kids) in schoolchildren on preventing obesity and improving academic achievement in children from 4 to 7 years with or without ADHD from Castilla-La Mancha, Spain.

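### After a summer-holiday washout, first-year intervention schools cannot be assumed to be back in a control state, yet year 2 is modelled alongside year 1 with no fixed baseline, no carryover provision and no analysis named as confirmatory

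*Protocol article*

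**What the plan says.** All references are to the Protocol article.

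- **Crossover.** Study intervention has schools swap arms, in both directions, "after a washout period (the summer holidays"). The Abstract also describes schools being crossed over in the second academic year.
- **Lasting components.** Study intervention lists, for the playgrounds, "Fixed (a balance circuit and panels with incentives to be physically active during break time) and mobile equipment". No section says what happened to this equipment when a school became a control. The parent and teacher level includes access to a blog, which Evaluation and follow-up says was available over the two years.
- **Measurement times.** Study variables and measurements gives three: "at the beginning and end of the first academic year (in September 2013 and June 2014", and then June 2015. Inclusion criteria, however, speaks of measurements at the start and end of each academic year, which would imply one at the start of year 2.
- **Analysis.** Statistical analysis fits mixed models to each outcome at the end of the first and of the second year. The named terms are baseline values, age, school and a 1/0 intervention indicator. It also refers to change between the intermediate and final evaluations. Under intention to treat, children stay in the group to which they were first assigned.
- **Sample size.** It targets a 2 % difference "in mean body fat at the end of the first year".
- **Carryover.** Discussion: "some carryover effect cannot be ruled out". No remedy follows.
- **Duration.** Study intervention also states: "The intervention was applied in the intervention group over two full academic years".

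**The concern.** In year 2 the control schools are those that had the programme in year 1. If the fixed equipment stayed, they were still exposed to part of the intervention. If any year-1 gain in aptitude or adiposity lasted through the summer, they also began year 2 from a shifted level. Without a measurement after the washout, neither could be checked.

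The plan does not settle what the year-2 comparison is. The baseline could be September 2013 or June 2014, and the group indicator could follow the current period or the original allocation. The sentence on two full academic years leaves open whether the original intervention group stopped at all. Only the sample size is tied to year 1, and nothing in the article ranks the year-1 result above the year-2 result. A year-2 estimate could therefore be reported as a primary result although its relation to the true effect is undetermined.

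**Working it through.** **Inputs from the document.** Difference 2 points of body fat at the end of year 1; alpha 0.05 (sidedness not stated, two-sided assumed); power 0.80; 140 children per group before inflation; inflation factor 1.1264; 800 per group; 15 % dropout; 21 schools.

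**Assumptions.** The SD of body fat is not given. The share r of the year-1 effect d still present in June 2015 in the schools treated first is not given either, and is varied from 0 to 1.

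**The plan's own figure.** With no SD, 140 cannot be reproduced, only inverted: SD = 2 × √(140/2) / (1.960 + 0.842) = 5.97 points. (The step to 1600 cannot be rebuilt, because the subgroup multiplier is not stated; this point does not need it.)

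**Year-2 contrast.** Let A be treated in year 1 and B in year 2. Relative to no treatment:

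| | June 2014 | June 2015 |
|---|---|---|
| A | d | rd |
| B | 0 | d |

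Currently treated minus currently control, that is B minus A, in June 2015:

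- against the September 2013 baseline: d - rd = (1 - r)d
- as change from June 2014: (d - 0) - (rd - d) = (2 - r)d
- adjusted for June 2014 with regression slope b: (1 - r + b)d, which lies between these two when b is between 0 and 1

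Coded by original group (A minus B), September 2013 baseline: -(1 - r)d.

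With d = 2.0:

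| r | Sept 2013 baseline | Change from June 2014 | Adjusted for June 2014, b = 0.7 (assumed) | Original-group coding, Sept 2013 baseline |
|---|---|---|---|---|
| 0 | 2.0 | 4.0 | 3.4 | -2.0 |
| 0.25 | 1.5 | 3.5 | 2.9 | -1.5 |
| 0.5 | 1.0 | 3.0 | 2.4 | -1.0 |
| 0.75 | 0.5 | 2.5 | 1.9 | -0.5 |
| 1 | 0 | 2.0 | 1.4 | 0 |

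The first version is unbiased only at r = 0, the second only at r = 1. If d = 0, every entry is 0.

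**Year 1 alone.** At June 2014 no school has crossed over, so r does not enter. Completers: 800 × 0.85 = 680 per arm; 1360 / 21 = 64.8 per school. Design effect = 1 + 63.8 × ICC; SE = 5.97 × √(2 × design effect / 680).

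| ICC (assumed) | Design effect | SE | Power, normal | Power, t with 19 df |
|---|---|---|---|---|
| 0.01 | 1.64 | 0.41 | >0.99 | >0.99 |
| 0.02 | 2.28 | 0.49 | 0.98 | 0.97 |
| 0.05 | 4.19 | 0.66 | 0.85 | 0.82 |

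At this school size, the plan's factor of 1.1264 corresponds to an ICC of 0.1264 / 63.8 = 0.002, so the table covers values well above the one planned for.

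**The case against.** The year-1 comparison is already planned, is untouched by carryover, and is the one the sample size serves. The text reads most naturally as one model per year, so no period term is needed within a year, and no pooled two-period estimate is described. An article may leave the ranking of analyses to a fuller document. The two-academic-years sentence may mean only that the programme ran in both years, in whichever schools were then due for it. The intention-to-treat sentence is chiefly about attendance.

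Much of this stands, and it limits the point. Three stronger readings are tempting, and the document does not support them:

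- *That the schools cannot return to a control state.* The missing statement on equipment is in the text. Lasting learning or adiposity effects are an inference, and the article says only that carryover is possible.
- *That year-2 or pooled results are pulled towards no effect by a known amount.* That holds for the September 2013 baseline. As change from June 2014, the same carryover leaves an overestimate unless r = 1.
- *That there was certainly no September 2014 measurement.* The schedule lists none, but Inclusion criteria implies one.

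The objection does not dispose of the rest. The article itself commits to modelling year 2, mentions change from the intermediate evaluation, concedes carryover, and makes statements about duration and group coding that do not fit the crossover as worded. These are defects in what is written, not detail left out for brevity.

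**Conclusion.** The concern holds as a matter of design and of what is fixed in the plan. First-year intervention schools cannot be assumed to be controls again in year 2, and the article does not determine what its year-2 contrast estimates. For a true effect of 2.0 points, that contrast ranges from 4.0 down to 0 depending on the baseline and on r, and from -2.0 to 0 if original-group coding is applied on the September 2013 baseline. This rests on an assumed range for r and on the same one-year effect d in both periods. It does not show that carryover occurred, and it does not touch the year-1 randomized comparison. With no true effect there is nothing to carry over, so what is at risk is the estimate and the power when an effect exists. The matter should be settled before any year-2 result supports a primary conclusion.

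**What to change.** 1. Name the randomized parallel comparison at June 2014, adjusted for the September 2013 baseline, as the confirmatory analysis. This matches the time point of the sample size.
2. Label year-2 results, and any two-period estimate, as supportive. Code treatment by period, include a period term in any two-period model, state the baseline, and show the possible carryover bias for that baseline over r from 0 to 1.
3. Reconcile with the crossover described in the Abstract and Study intervention: the sentence on two full academic years, the original-group rule in Statistical analysis, and the measurement times in Inclusion criteria as against Study variables and measurements.
4. Record, school by school, which intervention components remained in place in year 2.

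The cost is mainly wording, plus one record per school. The primary claim gives up whatever efficiency the crossover might have added. At the back-solved SD of 5.97, with 680 completers per arm in 21 schools, year 1 does not need it for the planned difference: power is about 0.82 (t, 19 df) to 0.85 (normal) at an ICC of 0.05, and higher at smaller values.
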